# Rationale and design of the SMILe (Spinal Morphine or Intravenous Lidocaine) study: protocol for a multicentre randomised clinical trial in southern Sweden on whether spinal morphine improves postoperative recovery compared to intravenous lidocaine in patients undergoing robot-assisted upper urinary tract surgery

**DOI:** 10.1136/bmjopen-2025-113402

**Published:** 2026-05-06

**Keywords:** Anaesthesia in urology, CLINICAL PHYSIOLOGY, Hemodynamics, Patient Reported Outcome Measures, PAIN MANAGEMENT, Randomized Controlled Trial

## Abstract

**Introduction:**

Robot-assisted laparoscopic surgical procedures are commonly perceived to result in fast recovery; however, the postoperative course can be challenging for many patients. We have previously found severe pain and a significant decrease in the patient-reported outcome measure Quality-of-Recovery 15 (QoR-15) in a cohort of patients undergoing robot-assisted upper urinary tract surgery. In similar settings, intrathecal analgesia is sometimes used to improve recovery; however, its benefits have not been established. Therefore, this study aims to examine the effects of intrathecal analgesia in this setting compared with an active comparator intravenous lidocaine.

**Methods and analysis:**

In this randomised, assessor-blinded multicentre trial, 220 patients scheduled for robot-assisted upper urinary tract surgery under general anaesthesia are recruited after obtaining informed consent. They are randomised to receive either intrathecal analgesia or an intraoperative infusion with lidocaine. The primary study outcome is the decrease in QoR-15 from baseline to postoperative day 1. Other outcomes of interest include postoperative pain, length of stay and postoperative complications. Differences in intraoperative haemodynamics and postoperative inflammatory parameters will also be analysed.

**Ethics and dissemination:**

This study has been approved by the Swedish Medical Products Agency (5.1.1-2023-69740 and 5.1.2-2025-030145). The results of this study will be presented at national and international meetings and submitted for publication in peer-reviewed international medical journals.

**Trial registration number:**

NCT06349668.

STRENGTHS AND LIMITATIONS OF THIS STUDYMulticentre design increases external validity.Use of active comparator increases clinical benefit of key results.Recovery is measured in multiple ways at multiple time points, as are effects on haemodynamic and inflammatory parameters.Double-blind set-up not possible.Absence of control group with no treatment.

## Introduction

 Robot-assisted laparoscopic surgery is associated with a reduction in surgical trauma compared with laparotomy. This leads to less bleeding and faster patient recovery.^1^ However, patients who undergo laparoscopic surgery may experience more pain during the first day than patients who have undergone the same procedure with open technique.^2^ In our own material, we have noted severe postoperative pain in a majority of patients who underwent robot-assisted laparoscopic upper urinary tract surgery (unpublished data).

In the case of major open abdominal surgery, in addition to general anaesthesia, epidural analgesia is considered standard of care to enable adequate postoperative pain relief.^3^ In laparoscopic surgery, however, the benefit of epidural analgesia is limited.^4 5^ Spinal (intrathecal) analgesia could be an option in laparoscopic surgery.

In abdominal surgery, spinal analgesia is most commonly applied using two components. Bupivacaine, a local anaesthetic, has a relatively short (2–6 hours) duration of action after administration and is effective mainly during surgery, and morphine, which has a longer duration of action and provides pain relief up to 24 hours postoperatively. This mixture will henceforth be referred to as ‘morphine spinal’.

Morphine spinal has several disadvantages: it must (in many countries) be administered by an anaesthesiologist and can delay the start of surgery, it can cause perioperative hypotension as well as postoperative nausea and troublesome itching. In very rare cases, the method can lead to severe neurological complications caused by local bleeding or infection.^6^ Respiratory depression also is a known complication of morphine spinal.^7^ These findings suggest that an alternative pain relief strategy that is as effective as morphine spinal but lacks its disadvantages would be preferable.

Potential candidates for this alternative strategy include drugs such as non-steroidal anti-inflammatory drugs (NSAIDs), cyclooxygenase (COX)-2 inhibitors, clonidine, lidocaine, ketamine and magnesium.^8 9^ However, their effectiveness has not been definitively established,^10^,^12^ some preparations are not available in Sweden (nefopam and metamizole) and there is also uncertainty about possible negative effects related to kidney function (NSAIDs and COX-2 inhibitors) and malignancy (ketamine, clonidine and magnesium).^13^,^20^ This is of great importance in patients undergoing upper urinary tract surgery since they are often affected by malignant kidney disease.

The only alternative adjunctive treatment that is considered to have the possibility of approaching an equivalent effect to morphine spinal and that is not associated with renal deterioration or a negative effect on tumour progression is intravenous administration of lidocaine.

Lidocaine is a local anaesthetic that has been used since the 1950s. Lidocaine can, among other routes, be given intravenously, epidurally and as infiltration anaesthesia.^21^ When administered intravenously, lidocaine can reduce pain, counteract hyperalgesia and dampen the inflammatory response during surgery,^22 23^ and is thus a possible strategy to improve patient recovery after abdominal surgery.^24 25^ A meta-analysis examining the effect of intravenous lidocaine in laparoscopic surgery showed that lidocaine resulted in a reduced need for opioids, less pain and less postoperative nausea.^26^ However, a Cochrane analysis from 2018 examining the effect of intravenous lidocaine in all types of surgery showed only a small effect on pain early (0–4 hours) postoperatively.^10^

The evidence for the benefits of intravenous lidocaine in urological laparoscopic surgery is sparse. In open kidney surgery, there was less need for opioids, less pain during movement and less postoperative nausea.^27^ A three-arm study comparing intravenous lidocaine with a spinal anaesthetic (with the local anaesthetic bupivacaine and the opioid fentanyl) or a so-called TAP (transabdominal plane) blockade in prostatectomies (both open and robot-assisted) showed no difference in postoperative recovery.^28^ Lauwick *et al.* reported that patients receiving intravenous lidocaine required less opioids and performed better on a functional walking test the day after a robot-assisted prostatectomy.^29^ In laparoscopic renal surgery, a randomised trial showed no improvement with lidocaine infusion in terms of pain, opioid requirement or length of stay.^11^ In contrast, a retrospective observational study showed a reduction in opioid requirement, less pain and faster recovery of bowel function after the introduction of intravenous lidocaine in patients who underwent laparoscopic nephrectomy.^30^

The benefit of combining general anaesthesia with morphine spinal is expected to be primarily visible through an effect on so-called ‘patient-reported outcome measures’ (PROM). The importance of using these patient-centred outcome measures when trying to improve perioperative care has recently been described.^31^ Quality-of-Recovery 15 (QoR-15), one of the several tests based on PROM, is often recommended as a recovery outcome measure in clinical trials.^32 33^

The QoR-15 measures patient recovery after surgery in the five domains of pain, physical well-being, physical independence, psychological support and emotional status. The QoR-15 provides a more complete picture of patient recovery compared with, for example, focusing solely on pain, and can be used to measure the quality of perioperative care.^34^ A change of 6–8 points has been defined as the minimal clinically important difference (MCID).^35 36^ Alternatively, a QoR-15 value of 118 has been indicated as the lowest value associated with an acceptable level of postoperative recovery (patient-accepted symptom state).^35^

In addition to providing pain relief, a morphine spinal also blocks the sympathetic nervous system, which through arterial and venous vasodilatation frequently results in low blood pressure. On the other hand, robot-assisted laparoscopic surgery itself stimulates the sympathetic nervous system, which results in increased blood pressure.^37^ It has not been studied how low blood pressure should be treated in a patient with a morphine spinal undergoing robot-assisted laparoscopic surgery. More knowledge about this enables a physiologically correct treatment, which is important especially when caring for patients with cardiovascular diseases who undergo robot-assisted laparoscopic surgery.

The surgical procedure is a critical event for cancer patients, as small parts of the tumour might spread into the bloodstream. A disturbed immune system, due to, among other factors, the inflammatory reaction caused by the surgical trauma and pain, can increase the risk of these small tumour parts developing into metastases.^38^ In surgery for benign conditions, a strong inflammatory response can have a negative impact on wound healing and increase the risk of complications. The effect of morphine spinal on the sympathetic nervous system affects the inflammatory response of the body to surgery, which in turn can be of importance to the risk of recurrence in cancer surgery.^39^ Morphine also has direct effects on the immune system, which can affect the recovery and recurrence rate of cancer.^40^ It is therefore of interest to compare different inflammation markers in patients with or without morphine spinal.

We therefore aim to compare the effects of a morphine spinal on recovery and well-being with intraoperative lidocaine infusion in patients undergoing robot-assisted upper urinary tract surgery. In a subgroup, the haemodynamic and inflammatory effects of both treatments are studied.

## Methods and analysis

### Study design, setting and population

This is a randomised prospective phase III (therapeutic confirmatory) multicentre study. The trial population consists of patients undergoing robot-assisted laparoscopic upper urinary tract surgery. The trial will start at the University Hospital in Linköping, Sweden. After the start of the study, other Swedish hospitals will be invited to participate in the trial.

Inclusion and exclusion criteria for participation in the trial are shown in table 1.

**Table 1 T1:** Inclusion and exclusion criteria

Inclusion criteria	Exclusion criteria
The patient is listed for planned robot-assisted laparoscopic surgery on kidney and/or ureter at one of the hospitals participating in the trial The patient agrees to participate in the trial by signing ‘Informed consent’ after having received written and oral information	Anaesthetic risk classification (ASA) ≥4 Patients who are minors or declared incompetent, who have a severe psychiatric illness or cannot be expected to be able to understand the written and oral trial information due to severely impaired vision, hearing, cognition, reading ability or insufficient knowledge of Swedish Female patients who are pregnant or breastfeeding Premenopausal female patients who have not undergone sterilisation, hysterectomy, bilateral salpingectomy and/or bilateral oophorectomy, and who are not using highly effective contraception with low user dependence, and where there is no negative pregnancy test Emergency procedure Research staff is not available Extensive surgery on another organ during the same procedure The responsible anaesthesiologist recommends spinal or epidural analgesia Contraindications to morphine spinal, such as coagulopathy, previous back surgery with osteosynthesis material or severe aortic valve stenosis, or there is reason to expect a difficult puncture, such as pronounced scoliosis or pronounced obesity Contraindication to lidocaine infusion: proven allergy to local anaesthetics, renal failure with eGFR <30, liver failure due to acute hepatitis or cirrhosis corresponding to Child-Pugh ≥B, severe arrhythmia or heart failure problems (corresponding to NYHA IIIb or higher) and myasthenia gravis Previous participation in the trial

ASA, American Society of Anesthesiologists; eGFR, estimated glomerular filtration rate; NYHA, New York Heart Association.

### Patient and public involvement

This study was launched based on the finding of significant postoperative pain and discomfort reported by patients undergoing robot-assisted laparoscopic upper urinary tract surgery. The primary outcome of the study is based on the QoR-15 score, a PROM. Routines for patient recruitment and data collection have been modified to minimise patient discomfort related to the trial. Otherwise, patients have not been directly involved in the design and will not be directly involved in the recruitment to and conduct of the trial. Patients who require so will be informed of the results of the study, otherwise they are not involved in planning for the distribution of study results.

### Recruitment and consent

At the anaesthesia visit before surgery or at another time before surgery, the anaesthesiologist examines whether the potential subject meets the inclusion criteria and has no exclusion criteria. Potential trial subjects receive oral and written information about the trial and are asked after a period of consideration for participation. This includes information on data use and the handling of blood samples. Consent to participate in the trial is given verbally as well as in writing and is obtained by an anaesthesiologist.

### Inclusion and randomisation

Test subjects are included consecutively. Randomisation of the participating subjects takes place after inclusion in the trial, before the start of anaesthesia. For each participating hospital (apart from US Linköping, see the next section), Forum Östergötland prepares before the start of the trial 100 sequentially numbered, opaque and sealed envelopes in series of 20 with both groups distributed 1:1. For US Linköping, 200 envelopes are prepared in the same way. Forum Östergötland retains the randomisation codes.

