### Blinding

Blinding of the subject and the anaesthesiologist in charge of the patient is not performed. Group allocation is not recorded in the CRF (case record file), only a checkbox with ‘Has the patient received the planned treatment (morphine spinal or lidocaine infusion) as planned yes/no’. The spinal analgesia or lidocaine infusion is documented on the randomisation paper which is kept separately from the CRF. Spinal analgesia or lidocaine infusion is also documented in the usual way in the anaesthesia journal. This information is visible when trial data are transferred from the anaesthesia record to the CRF but not later during data analysis. When the subject is contacted postoperatively, it should not be actively sought whether the subject has received a spinal anaesthetic or not. Should this information still come to light, no note is made of this. However, if the person who collects the QoR-15 on POD 1 has, for some reason, received information about the treatment method before the QoR-15 has been recorded, this must be recorded on the PD (protocol deviation) log. Group affiliation is not noted in the diary. The randomisation code is broken only when data acquisition is completed. In case of emergency, code breaking takes place through a review of the subject’s anaesthesia record.

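### Fixed, published blocks of 20 per hospital make some assignments predictable where anaesthesiologists recruit and treating staff are unblinded; the risk is modest and varied, undisclosed large blocks would largely remove the certain cases

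*Protocol article*

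**What the plan says.** Under Inclusion and randomisation, Forum Östergötland prepares for each hospital "100 sequentially numbered, opaque and sealed envelopes in series of 20 with both groups distributed 1:1". For the lead site, "For US Linköping, 200 envelopes are prepared in the same way". No variation in the size of the series is mentioned. On timing, "Randomisation of the participating subjects takes place after inclusion in the trial, before the start of anaesthesia", and on custody, "Forum Östergötland retains the randomisation codes". The same section says that subjects are included consecutively.

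Three other sections bear on this:

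- **Blinding:** "Blinding of the subject and the anaesthesiologist in charge of the patient is not performed". The treatment given is also written in the ordinary anaesthesia record.
- **Recruitment and consent:** an anaesthesiologist checks eligibility, and "Consent to participate in the trial is given verbally as well as in writing and is obtained by an anaesthesiologist".
- **Table 1 (exclusion criteria):** one criterion is "The responsible anaesthesiologist recommends spinal or epidural analgesia". Others are an expected difficult puncture and the absence of research staff.

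The article is dated 6 May 2026. Trial status reports 54 patients included by 1 October 2025 and expects recruitment to end at the close of 2027.

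**The concern.** Opaque sealed envelopes stop anyone reading the next assignment. They do not stop anyone inferring it. If each series of 20 holds exactly ten of each arm, a running count of past treatments gives the odds for the next envelope, and once one arm is used up the rest of the block is known.

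To exploit this, a person needs sight of past assignments, a role in recruitment, and some discretion over who enters. The anaesthesia record offers the first. Anaesthesiologists screen and take consent, and several exclusions turn on their judgement before the envelope is opened.

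At stake is the comparability of the groups. The primary outcome is a patient-rated score, compared by a rank-sum test. If patients expected to recover well were steered towards one arm, the difference in expected recovery would pass into the estimated effect.

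**Working it through.** **Inputs.** Block of 2m = 20 with m = 10 per arm (Inclusion and randomisation, reading 1:1 as exact within each series). Target difference 8, variance 400 (SD 20), 100 per group, 80% power (Calculation of sample size). Two-sided 5% (Analysis groups).

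**The plan's own figure.** n = 2 × (1.960 + 0.842)² × 400 / 8² = 98.1, so 99 per group. The t-test solution is 99.08, so 100. The stated 100 is reproduced and does not depend on the block design.

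**Predictability of a fixed 10:10 block, given a full tally**

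- Expected number of certain assignments at the block end: 2m/(m+1) = 20/11 = 1.82, or 9.1% of 20. A simulation of 200,000 blocks gave 1.817.
- Probability that the last k are all certain: 2 × C(20−k, 10) / C(20, 10). This is 100% for k = 1, 47% for k = 2, 21% for k = 3 and 8.7% for k = 4.
- Expected correct guesses when always naming the arm that is behind: m + (4^m / C(2m, m) − 1)/2 = 12.34 of 20, or 61.7%.
- If all blocks are filled, certain assignments number about 18 of 200 at the lead site, 9 of 100 at another hospital, and 20 of 220 overall.

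**Possible bias (the shift s is an assumption).** Suppose enrolled patients guessed to get one arm have expected QoR-15 higher by s, and those guessed to get the other arm lower by s. With a proportion p of correct guesses, the arm difference is biased by 2s(2p − 1). If only certain assignments are acted on, it is biased by 2s × 1/11. The standard error is 20 × √(2/100) = 2.83. Type I error is for a single two-sided test, by normal approximation.

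| Behaviour | Shift s | Bias (points) | Type I error |
|---|---|---|---|
| Certain assignments only | 4 | 2 × 4/11 = 0.73 | 5.8% |
| A quarter of all guesses | 4 | 1.87/4 = 0.47 | 5.3% |
| Every guess | 2 | 0.467 × 2 = 0.94 | 6.3% |
| Every guess | 4 | 0.467 × 4 = 1.87 | 10.1% |

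Here 0.467 = 2 × (2 × 0.617 − 1), computed from the unrounded proportion. The bias is linear in s.

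**Alternative schemes.** These were simulated for a recruiter who knows the set of block sizes but not their order or where blocks end.

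| Scheme | Certain | Best guess correct |
|---|---|---|
| Fixed 20 | 9.1% | 61.7% |
| Mix of 16/20/24 | about 1.0% | about 61% |
| Mix of 20/30/40 | about 0.9% | about 59% |
| Mix of 4/6/8 | about 2.4% | about 68% |

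A recruiter who does not know the set of sizes would do no better than this.

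**The case against.** **The candidate's envelope may not be known.** Eligibility and consent can come well before surgery, and Analysis groups allows up to 12 months from inclusion to surgery. If envelopes are opened close to surgery, patients already waiting may take earlier numbers. Consecutive inclusion narrows the scope further. This stands: the certainty figures apply only to someone who knows which envelope the candidate will receive.

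**A full tally is assumed.** A reader might infer that every recruiter knows every past assignment. The article does not say so. It does not say that the consenting and the treating anaesthesiologist are the same person, allocation is kept off the case record form, and at 54 patients in about 18 months a block spans a long period. This also stands, although the anaesthesia record makes a tally possible.

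**The larger bias is near worst case.** A shift of 4 points either way is an 8-point swing between patients guessed to each arm, equal to the whole target difference, and it is applied to every guess. This stands, so the smaller figures must be read beside it.

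**The remedy barely alters average guessing.** Under the same extreme assumption, 59.3% correct gives 2 × 4 × (2 × 0.593 − 1) = 1.49 points and about 8.2% type I error, against 1.87 points and 10.1%. This stands. A block of 20 is already harder to guess than small blocks, and the gain lies in removing the certain assignments.

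**Further readings the article does not support:**

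- That the trial is open-label throughout. It is described as assessor-blinded; the point needs only unblinded clinical staff.
- That 166 patients (220 − 54) remain after publication. That count is at 1 October 2025, so the number left in May 2026 is unknown.
- That no analysis could help. Baseline QoR-15 is collected, so adjustment could remove part of any selection, but not selection on unmeasured prognosis.

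**Conclusion.** The point holds as a modest weakness in allocation concealment. The fixed size, the separate stock per hospital, the unblinded treating staff, the recruiting role of anaesthesiologists and the discretionary exclusions are all stated, and publication during recruitment makes the block size available to anyone.

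With a full tally and a known envelope position, 9.1% of assignments are certain and 61.7% can be guessed. Under the assumed 4-point shift the bias runs from about 0.7 points (certain assignments only) to about 1.9 points (every guess), which is 9% to 23% of the 8-point target, and it is proportionately less for a smaller shift. These figures rest on exact 10:10 balance in each series and on the assumed shift, which the documents do not give.

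A reader might go further and infer that assignments have been steered or that the primary comparison is already compromised. Nothing in the article supports that. The case for acting is that the exposure is avoidable at small cost in a trial meant to be confirmatory.

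**What to change.** Have Forum Östergötland replace the unused envelopes with a list built from randomly varying, undisclosed, large block sizes, for example 20, 30 and 40 within each site. Sites that have not yet started should use it from the outset. Sites already recruiting should ideally switch once their current block is complete, so that no block is cut short. Only that unit should hold the block scheme, and site-facing documents should omit it. Small mixed blocks such as 4/6/8 should be avoided, since they raise correct guessing to about 68%.

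The cost is one new list and envelope set per site from the unit that already makes them, and a protocol modification notified to sites. The Ethics section requires approval in CTIS if the change counts as substantial. Imbalance within a site could be slightly larger, with negligible loss of power.
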